### Outcomes and Measures

Validated screening scales for self-reported symptoms will be used to assess clinical outcomes. These include the Mental Health Literacy Scale [69], the Generalized Anxiety Disorder 7-item (GAD-7) Scale (a GAD-7 score of ≥10 indicates moderate to high anxiety) [70], the Perceived Stress Scale (PSS-10) (a PSS-10 score of ≥10 indicates likely moderate to high stress) [71], the Brief Resilience Scale (BRS; BRS mean scores ranging from 1.00 to 2.99 indicate low resilience, scores from 3.00 to 4.30 suggest normal resilience, and mean scores from 4.31 to 5.00 suggest high resilience) [72,73], and the Patient Health Questionnaire-9 (PHQ-9; a score of ≥10 indicates moderate to high depression) [74]. Burnout will be assessed using the Maslach Burnout Inventory (MBI), specifically the MBI-Educators Survey, for use with educators [75,76]. An exploratory outcome will be to evaluate the acceptance of the Wellness4Teachers program by teachers in Zambia, which can be measured by the proportion of the target population (teachers in Livingstone, Lusaka, Kasama, and Solwezi) who subscribe to the program. Primary outcomes for this study will be changes in mental health literacy and the prevalence of moderate to high stress, burnout, moderate to high anxiety, moderate to high depression, and low resilience from baseline to 6 weeks, 3 months, 6 months, and 12 months among the subscribers of the Wellness4Teachers Zambia program. Secondary outcomes include the mean score on the Mental Health Literacy Scale and the prevalence of moderate to high stress, burnout, moderate to high anxiety, moderate to high depression, and low resilience at baseline in subscribers of the Wellness4Teachers email messaging program. Other secondary outcome measures will include changes in mean scores on the PSS-10, MBI, GAD-7, PHQ-9, and BRS. In addition, sociodemographic factors, work-related factors, and mental health literacy correlate with moderate to high stress, burnout, moderate to high anxiety, moderate to high depression, and low resilience at baseline among subscribers of the Wellness4Teachers program.

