### Statistical Analysis

SPSS (version 25; IBM Corp) [80] will be used to analyze the quantitative data from the surveys. Surveys with more than 50% missing responses will not be included in the data analysis. There will be no missing data imputation, and the analysis of the included survey responses and results will be based on completed survey data. Descriptive statistics for demographic, mental health literacy, clinical, and burnout-related variables will be provided. A 2-tailed *P*≤.05 will be used to determine statistical significance for all analyses, and descriptive characteristics will be presented as percentages and numbers. A chi-square test and logistic regression analysis will be used to separately identify demographic, clinical, and work-related correlates of anxiety, depression, stress, low resilience, and burnout for elementary and high school teachers. Significant and borderline significant variables from the chi-square analysis would be used to develop multivariable binary logistic regression models to predict the adjusted odds of outcomes for the exposure of interest and each potential correlate. The impact of the email supportive messaging program in reducing moderate to high anxiety, moderate to high depression, moderate to high stress, burnout, and improving resilience among subscribers will be evaluated by comparing the mean changes in these parameters from baseline to 6 weeks, 3 months to 6 months, and 12 months using the paired *t* test. To assess the effects of the intervention against a control group, we will choose a defined period of 3 months during the study period (for instance, the beginning of January 2023 to the end of March 2023) and compare the prevalence and mean scores on standardized scales for stress, anxiety, burnout, and depression at 6 weeks for subscribers who have received the daily supportive SMS text messages for 6 weeks (the intervention group) to the baseline prevalence and mean scores on the same scales for new subscribers during the period (the control group).

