## Results

The Wellness4Teachers email messaging program is anticipated to be launched in January 2023. Enrollment will continue for 12 months, and data collection will continue for another 12 months. Results of the study will be disseminated to stakeholders in the education sector in Zambia, East African countries, and globally through workshops, conference presentations, and peer-reviewed publications.

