### Conclusions

This study will provide vital information about mental health literacy and the prevalence and correlates of psychological problems among teachers in Zambia. The study will also provide evidence of the effectiveness of the email messaging program, Wellness4Teachers, in reducing psychological symptoms and improving mental health literacy among teachers. The knowledge from this study will significantly impact the promotion of mental health literacy and the management of stress, burnout, anxiety, depression, and low resilience among teachers. The study outcome will help inform policy decision-making for health care resource allocation in support of the educational sector in Zambia.

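### The control comparison covers only week 6, one unfixed 3-month window and four of six primary outcomes, although rolling enrolment would support it at 3 and 6 months

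*Protocol article*

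**What the plan says.** Outcomes and Measures defines the primary outcomes as changes in mental health literacy and in the prevalence of stress, burnout, anxiety, depression and low resilience "from baseline to 6 weeks, 3 months, 6 months, and 12 months among the subscribers of the Wellness4Teachers Zambia program".

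Statistical Analysis gives two routes to an effect.

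- The first is within-person, "comparing the mean changes in these parameters from baseline to 6 weeks, 3 months to 6 months, and 12 months using the paired" *t* test.
- The second is a control comparison: "we will choose a defined period of 3 months during the study period", with January to March 2023 as an example. It will "compare the prevalence and mean scores on standardized scales for stress, anxiety, burnout, and depression at 6 weeks" in teachers who have had six weeks of messages and set these against "the baseline prevalence and mean scores on the same scales for new subscribers during the period (the control group").

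Results gives the timetable: "The Wellness4Teachers email messaging program is anticipated to be launched in January 2023", and "Enrollment will continue for 12 months, and data collection will continue for another 12 months". Data Collection has every subscriber surveyed on enrolment and again at each of the four follow-up times. Conclusions states: "The study will also provide evidence of the effectiveness of the email messaging program".

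**The concern.** The protocol accepts that before-after change alone does not show an effect, because it builds a control group from new subscribers. It then restricts that comparison in three ways: one time point, one window not fixed in advance, and four of the six primary outcomes. Everything else rests on change within self-selected subscribers, with nothing to show how scores would have moved without the programme.

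At stake is the reading of the 3-, 6- and 12-month results. A secular trend over the study period would be counted as programme effect. So would a seasonal difference, if enrolment or response bunches in parts of the year. A window left open until data exist also leaves room for a choice influenced by results. Most of the data that could serve the authors' own control method would go unused.

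**Working it through.** **Coverage.** Six primary outcomes at four follow-up times give 6 x 4 = 24 outcome-by-time results. The control comparison covers stress, anxiety, burnout and depression at 6 weeks, so 4 of 24. The other 20 have no comparator. The sentence on paired tests does not name mental health literacy, and as worded it does not clearly list baseline to 3 months.

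**Inputs.** Enrolment lasts 12 months (Results). The plan expects 993 completed baseline surveys (Sample Size Estimation), and hypothesises a reduction of at least 20%, read here as relative (Hypothesis). Assumed, because the document gives no figure: uniform accrual, a 30% baseline prevalence, and the follow-up response rates below.

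**The plan's own figure.** The document gives no power for any effect comparison; 993 is a precision target for baseline prevalence. With z = 1.96, p = 0.5 and a 3% margin, n0 = 1067. The finite population correction for 30,561 teachers gives 1067/(1 + 1066/30,561) = about 1031, not 993. Using 14,205, the Lusaka teachers alone (10,822 + 3383), gives 993. The step 993/0.20 = 4965 is right. This is a separate matter. I keep 993 because the plan uses it, and 1031 would raise the counts below by only about 4%.

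**Concurrent baselines.** Enrolment is still open for (12 - follow-up month) months while earlier subscribers reach a given follow-up. The number of concurrent baselines is 993 x that figure / 12.

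| Follow-up | Months of overlap | Share of enrolment | Baselines |
|---|---|---|---|
| 6 weeks | 10.5 | 87.5% | 869 |
| 3 months | 9 | 75% | 745 |
| 6 months | 6 | 50% | 497 |
| 12 months | 0 | 0% | 0 |

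One 3-month window holds 993 x 3/12 = 248 baselines. In the January to March 2023 example, which starts at launch, only teachers enrolled in the first six weeks can reach week 6 inside the window: 993 x 1.5/12 = 124 at full response. The months of overlap depend only on the length of enrolment. The counts also need uniform accrual.

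**Power for 30% against 24%** (30% x 0.8 = 24%, two-sided 0.05). Power = Φ[(0.06 - 1.96 SE0)/SE1], where SE0 uses the pooled proportion and SE1 the two separate proportions.

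| Comparison | Control v treated | SE0, SE1 | Power |
|---|---|---|---|
| One window, equal groups | 248 v 248 | 0.0399, 0.0398 | 32% |
| January to March example | 248 v 124 | 0.0494, 0.0481 | 22% |
| Full period, 6 weeks, equal groups | 869 v 869 | 0.0213, 0.0212 | 80% |
| 3 months, 85% response | 745 v 633 | 0.0241, 0.0239 | 70% |
| 6 months, 85% response | 497 v 422 | 0.0295, 0.0292 | 53% |
| 3 months, 50% response | 745 v 372 | 0.0285, 0.0278 | 56% |
| 6 months, 50% response | 497 v 248 | 0.0349, 0.0340 | 40% |
| 3 months, 20% response | 745 v 149 | 0.0407, 0.0388 | 30% |
| 6 months, 20% response | 497 v 99 | 0.0499, 0.0476 | 21% |

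Using SE1 in both places gives 71% and 54% at 85% response, 58% and 42% at 50%, and 34% and 24% at 20%. These figures treat the groups as independent and ignore covariate adjustment.

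**The case against.** **Seasonality.** A reader might infer that any school-term pattern passes in full into the claimed effects at 3, 6 and 12 months. The document does not support that. If enrolment is uniform over 12 months, baselines and each set of follow-ups all cover every calendar month once, so a pattern that repeats yearly averages out of the pooled change. At 12 months each teacher answers in the same calendar month as at baseline, so such a pattern cancels within person whatever the accrual. What remains is a non-repeating trend and, at the earlier times, seasonality under uneven enrolment or response. The document gives no size for either.

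**Limits of the remedy.** It does not remove regression to the mean after self-referral. Follow-up responders are a selected subset compared with all new baseline responders, with no imputation. Early and late subscribers may differ, and at 6 months the treated come only from the first half of enrolment and the controls only from the second. The paired analysis at least holds the person fixed. All of this stands. Except for the complete cohort separation at 6 months, it applies to the authors' 6-week comparison too, so it is a reason to report limits rather than to keep the comparison narrow.

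**Power.** The 80% belongs to week 6 and should not be carried over to 3 or 6 months. Limitations warns that survey links sent by SMS usually draw under 20% response, and at that level power at 3 and 6 months is poor. The plan also compares mean scores, where one window does better: an assumed standardised difference of 0.25 with 248 per group has about 79% power.

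**Design and detail.** The study is declared quasi-experimental, its primary outcomes are changes among subscribers, and covariates are commonly left to an analysis plan. That is fair. But the article itself fixes the control comparison's time point, window length and outcomes, and these are what is questioned here.

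**Conclusion.** The point holds as an inexpensive improvement that should be made. Four of 24 primary results have a comparator. Low resilience and mental health literacy have none at any time, and no outcome has one at 3, 6 or 12 months. Rolling enrolment with a survey on entry supplies same-calendar-time baselines for 10.5, 9 and 6 months of accrual at 6 weeks, 3 months and 6 months, and none at 12 months. The gain in numbers over a single window is 869/248 = 3.5-fold at 6 weeks, 3.0-fold at 3 months and 2.0-fold at 6 months, given uniform accrual. The power figures also rest on the assumed prevalence and response.

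The document does not show that the uncontrolled results are biased by any particular amount, and the wider comparison would not turn this design into proof of effectiveness. It would address calendar-time effects and leave the other threats to be stated.

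**What to change.** Keep the paired analysis and change the control comparison as follows.

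- Use the whole 12-month enrolment period in place of one chosen window.
- Cover every primary outcome, including the Mental Health Literacy Scale and the BRS.
- Make the comparison at 6 weeks, 3 months and 6 months, setting follow-up responses against baselines of new subscribers in the same calendar month. Adjust for calendar month, city, school level and demographics. A teacher can be a control at baseline and treated later, so allow for repeated responses.
- Label the 12-month result as uncontrolled change.
- State that regression to the mean, selective follow-up response and early-versus-late subscriber differences are not removed, with no cohort overlap at 6 months. Limit the effectiveness statement in Conclusions accordingly.
- Correct the intervention-group definition in Statistical Analysis, which describes the messages as SMS texts although the programme is delivered by email.

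The cost is revised analysis wording and a little more modelling on data already planned. The downside is a weaker 12-month claim.

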## Methods

### Study Design

This will be an interventional study, specifically a quasi-experimental design, which will employ a quantitative longitudinal and cross-sectional survey methodology with data collected from subscribers of Wellness4Teachers email messaging service users.

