### Participants’ Recruitment and Subscription

Subscription to the Wellness4Teachers email messaging program will be initiated by individual teachers accepting an invitation to subscribe from the Lusaka Apex Medical University’s organizational account on the ResilienceNHope web-based application. The local principal investigator (CC) will work with the Zambian Ministry of Education, the Lusaka Teachers Association, district school boards, and heads of elementary and high schools to invite teachers to join the Wellness4Teachers email messaging program. Participants will be eligible for inclusion if they are school teachers and residents of Livingstone, Lusaka, Kasama, or Solwezi. Subscribers can unsubscribe from the program at any time by clicking the unsubscribe link associated with the messages. Based on the 10% dropout rate recorded for the Text4Hope program [51,52], the anticipated dropout rate for the email messaging program will be less than 15% [54].

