### Limitations

Like most studies, this one has some limitations. First, the supportive email messages will be delivered for 12 months, and the outcome measures will be evaluated at 6 weeks, 3 months, 6 months, and 12 months. It is not certain what the effects of the intervention would be if it were extended. It is also unclear if the benefits of the intervention would diminish with the cessation of daily email messages. Second, although standardized, the self-reported scales used to assess mental health variables, such as moderate to high anxiety, are not diagnostic. Third, it is possible that participants’ demographics in the study may not reflect the demographics of the teacher population in Zambia; hence, the study findings may not be generalizable to all teachers in Zambia. In addition, web-based surveys with survey links delivered through SMS text messages usually achieve a response rate of less than 20% [54,78,79,83-86], so it is possible that we may not achieve our desired sample size with an email messaging program. Despite these limitations, this study is the first to assess the prevalence and correlates of stress, burnout, anxiety, and depression among teachers in Zambia using an email messaging program. To our knowledge, this study is also the first worldwide to assess if daily supportive email messages and mental health literacy information delivered by email would effectively reduce the prevalence and severity of psychological symptoms and improve mental health literacy among teachers.

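### The only controlled comparison sets 6-week stayers who answered a follow-up survey against enrolment-survey respondents, so retention and response can create or hide an effect

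*Protocol article*

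**What the plan says.** The Study Design section calls the study "specifically a quasi-experimental design, which will employ a quantitative longitudinal and cross-sectional survey methodology", with data only from subscribers, so there is no randomised comparator. The Statistical Analysis section builds one from a chosen 3-month window. The intervention arm is measured at 6 weeks, and its results are compared "for subscribers who have received the daily supportive SMS text messages for 6 weeks (the intervention group) to the baseline prevalence and mean scores" of the control arm. The control arm supplies its "baseline prevalence and mean scores on the same scales for new subscribers during the period (the control group").

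The same section fixes which surveys count: "Surveys with more than 50% missing responses will not be included in the data analysis", and "There will be no missing data imputation, and the analysis of the included survey responses and results will be based on completed survey data".

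On leaving, the recruitment section states: "Subscribers can unsubscribe from the program at any time by clicking the unsubscribe link associated with the messages". It expects dropout below 15%. The sample size section applies a 20% completion rate to the baseline survey. The Limitations section says that web surveys of this kind "usually achieve a response rate of less than 20" per cent, but treats this as a threat to the sample size. Separately, it warns that participants may not resemble the teacher population. It does not discuss response as a source of bias in the control comparison.

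**The concern.** The two groups are selected differently. A teacher enters the intervention group only by remaining subscribed for 6 weeks and completing the 6-week survey. A control enters by completing one survey at enrolment. If staying or answering is related to symptoms, the groups differ even when the programme does nothing. Should symptomatic teachers be likelier to leave or ignore the second survey, the 6-week group looks healthier. If the less symptomatic lose interest first, a real benefit is hidden.

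Making the groups disjoint would not remove this, because 6-week responders would still be a selected set. This is the only analysis that sets the programme against a control, so a claim of effectiveness beyond before-after change would rest on it.

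**Working it through.** **Plan figures.** The article gives no sample size, power or 6-week response rate for this comparison. Its 20% completion rate belongs to the enrolment survey: 993 / 0.20 = 4965, as stated. Using 20% at 6 weeks is my assumption. The hypothesised effect is a reduction of at least 20%.

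**Step 1: how much selection matters.** Let p be the prevalence in the control sample, with no treatment effect. Let rr be the chance that a symptomatic teacher enters the 6-week sample divided by the same chance for a non-symptomatic teacher, relative to entry into the control sample. The observed 6-week prevalence is

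q = p·rr / (p·rr + 1 − p).

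Take p = 0.38 (the lower anxiety figure in the Background) and an assumed rr = 0.7. Then q = 0.266 / (0.266 + 0.62) = 0.300, a false reduction of 1 − 0.300/0.38 = 21%. With 20% responding overall and unfiltered controls, this means about 16% response in symptomatic and 23% in non-symptomatic teachers. The rr that yields a 20% false reduction is [0.8p/(1 − 0.8p)] / [p/(1 − p)]: 0.75 at p = 0.25, 0.71 at 0.38, 0.67 at 0.50 and 0.51 at 0.74. No rr is given in the documents.

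**Step 2: retention alone, as a bound.** If every leaver were symptomatic, q = (p − d)/(1 − d). At p = 0.38, d = 0.10 gives 0.311 (18% lower) and d = 0.15 gives 0.271 (29% lower). This is an extreme, not an expectation.

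**Step 3: what the sign and size depend on.** Simulation with no effect; baseline and 6-week scores bivariate normal with correlation 0.6; true prevalence 35% at both times; logistic response at 20% per survey, with odds multiplied by 0.8, 0.7 or 0.6 per SD of score. All of these are assumed. In settings B to E the controls are themselves filtered by enrolment-survey response, which lowers control prevalence to 28.6%, 25.1% and 21.3%.

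| Setting | 6-week prevalence | Apparent change against control |
|---|---|---|
| A. Controls unfiltered (35%); 6-week response depends on baseline score | 31.1 / 28.9 / 26.6% | −11 / −17 / −24% |
| B. Both filtered, not nested; response depends on current score | 28.6 / 25.1 / 21.3% | 0 / 0 / 0% |
| C. Both filtered, not nested; 6-week response depends on baseline score | 31.1 / 28.9 / 26.6% | +9 / +15 / +25% |
| D. 6-week responders a subset of baseline responders; response depends on baseline score | 27.5 / 23.5 / 19.5% | −4 / −6 / −9% |
| E. Subset as in D; 6-week response depends on current score | 25.1 / 20.0 / 15.0% | −12 / −20 / −30% |

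Implementations differ slightly at the edges (3 to 7% for D, 12 to 29% for E); I quote 29% as the largest false reduction. If the gradient is reversed in setting A (odds multiplied by 1.25 per SD), 6-week prevalence is 39% against 35%, a false increase of about 11%.

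**The case against.** The strongest reply is that the control group is also response-filtered. The 20% completion rate is applied to enrolment, and surveys go to subscribers at every time point. Nothing says that a 6-week respondent must have answered at baseline. If both surveys draw similar fractions for similar reasons, only retention differs, and setting B shows no bias. This stands. It removes any basis for giving a single size or sign, but it does not make the groups comparable, as settings C to E show.

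A second reply is that primary outcomes are changes from baseline among subscribers, and impact is also assessed by paired t tests. Those compare people with themselves, so a change in who answers does not by itself create an effect there. That is correct, but the paired analysis has no control and cannot stand in for the comparison at issue.

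A third is that adjustment or weighting may appear in a fuller document. A reader might infer from this section that an unadjusted analysis has been chosen. The article does not say so, and its silence is not a fault. What it does fix is who is compared, at which survey, on completed surveys without imputation. None of that prevents weighting or adjustment.

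**Conclusion.** The point holds as a structural weakness. The stated groups pass different filters, so the only controlled estimate mixes any programme effect with retention and follow-up response. Under the assumed gradients, with no true effect, the bias lies between about a 29% false reduction and a 25% false increase in prevalence, with zero possible.

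A reader might infer that the bias favours the programme and matches the hypothesised 20% reduction. The documents do not support that. The response gradient, the correlation, the 35% prevalence and the 6-week response rate are all assumed. Under setting A only the steepest of three gradients exceeds 20%, and setting C reverses the sign. Nor does the text say that 6-week responders are a subset of baseline responders. The change is worth making because it is cheap, not because a particular bias has been shown.

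**What to change.** 1. Among 6-week responders with a linked baseline survey (the paired t test already needs this link), weight back to the baseline-survey cohort they came from by the inverse probability of 6-week response, given baseline scores, school level, city and demographics. State how many 6-week responders have no baseline survey and so cannot be weighted.
2. Adjust the group comparison for demographic and work-related covariates.
3. Report baseline scores of 6-week responders against non-responders, so that the direction of selection can be seen.
4. As a sensitivity analysis, restrict controls to new subscribers who later answer at 6 weeks and are not also counted in the intervention group. The second condition matters: with a January 2023 launch and the example window of January to March 2023, 6-week responders in the window are themselves new subscribers in it. Without the condition, the restriction would largely recreate the paired before-after comparison.

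No new data are needed. Weighting widens intervals somewhat. The restricted analysis costs much more: if 20% of controls answer at 6 weeks, the standard error of the control estimate grows by √(1/0.20) = √5, about 2.2 times. Weighting corrects only for measured predictors. Where response follows the current score, as in setting E, part of the bias remains, so the results should be reported with that limit.
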